### Objectives {7}

The primary objective of this randomized clinical trial is to analyse the effect of VR stimulation on the incidence of delirium after admission to the ICU. Participants in the control group will receive the standard ICU care, while participants in the intervention group will additionally receive VR stimulation. We hypothesize that participants receiving the VR stimulation will have a lower incidence of delirium during their stay in the ICU, compared to the control group. The secondary objectives are to evaluate differences in movement patterns and intensity between the intervention and control groups and between participants with delirium and without delirium. We expect that these differences will be related to the different types of delirium (i.e. hyperactive, hypoactive, or mixed). Additionally, it is predicted that it will be possible to detect differences in movement patterns between groups and identify patterns indicating the presence or absence of delirium. Secondary objectives also include the evaluation of the effect of VR on duration of delirium. In this case, it is hypothesized that the duration of delirium will be shorter in participants receiving the VR stimulation compared to those in the control group.

Further objectives which will be addressed include (1) evaluating the effect of VR stimulation, identified by changes in physiological parameters; (2) evaluating how easily the VR stimulation can be provided to patients by critical care professionals; (3) describing differences in cognition, health-related quality of life, and functional independence between groups, using questionnaires; and (4) evaluating if VR reduces the need for pharmacological treatment of delirium.

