### Outcomes {12}

The primary outcome is delirium incidence, measured three times a day (morning, midday, and evening) by the Intensive Care Delirium Screening Checklist (ICDSC) as part of standard assessment. With the ICDSC, delirium is determined by consciousness, inattention, disorientation, hallucination, agitation or retardation, speech and mood, sleep/wake cycle disturbance, and fluctuation [19]. A unique incidence of delirium is counted once a patient reaches a score of ≥ 4, on a scale from 0 to 8 [20]. The entire period that a patient has a score ≥ 4 is considered as a single episode, and accordingly, counts only as a single incidence. The mean incidences of delirium per group will be looked at. The incidence of delirium is considered to be clinically relevant as it is known that patients who experience delirium while in critical care have worse long-term outcomes [4]. Furthermore, due to the possible influence of sedatives and analgesics on the incidence of delirium, both sedation and pain levels will be assessed every 2 h [5]. Consciousness and sedation will be measured using the Glasgow Coma Scale [21] and the Richmond Agitation Sedation Scale [22], respectively, and pain will be measured using the Numeric Rating Scale [23] and the Behavioural Pain Observation Tool [24].

As a secondary outcome, the duration of delirium will be evaluated per 8-h periods, or as needed, while patients are in the ICU. If the participant is assessed as delirious via the ICDSC during any of the assessments during an 8-h span, the entire period will count as delirious. Duration of delirium is clinically relevant knowing that the duration of delirium is an independent predictor of mortality 6 and 12 months post-ICU admission [25, 26].

Additional secondary outcomes include the pattern and intensity of movements, before and during delirium as well as between groups, measured continuously during the ICU stay. The fact that patients in delirium have fluctuating motor performance movement patterns, differing from baseline, could be a possible marker for delirium detection [27]. Therefore, acceleration will be measured with wearable sensors such as inertial measurement units, which have been previously used successfully in the ICU [28]. The monitoring of patients’ movement patterns could provide a means of early detection of delirium, permitting early intervention by the care staff.

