## Data collection and management

### Plans for assessment and collection of outcomes {18a}

The study starts within 24 h after admission to the ICU. In the enrolment phase, participants will be randomly assigned to either the intervention or the control group, with the intervention beginning as soon as possible following enrolment. Three times a day (between 7:00 am and 7:00 pm) for 30 min, participants in the intervention group will receive the intervention (VR stimulation) applied directly in the bed. The intervention will be included in the daily schedule of the patients. The intervention period ends when the patient is discharged from the ICU or at the latest 14 days after admission to the ICU. Thus, the intervention period depends on the length of stay in the ICU and can vary between participants.

After allocation, incidence and duration of delirium is assessed in three shifts a day. If delirium is diagnosed, the standard ICU delirium therapy (local delirium protocol) will be started, regardless of the participants’ group. VR stimulation will optimally start before this time point. Delirium is assessed using the ICDSC which is a reliable (Cohen’s kappa (*κ*) = 0.60) [33] and specific (95%) [33] tool to detect delirium in ICU patients [5] and was translated into German by Radtke et al. [34]

Assessment of sedation will be done using the Richmond Agitation Sedation Scale which has a reliability of *κ* = 0.91 and a face validity with 81–92% agreement [22, 35]. Consciousness will be evaluated according to the Glasgow Coma Score which was originally found to have a *κ* = 0.66–0.77 for the whole scale, but has since been found to have higher reliability when looking at the eye, motor, and verbal scales individually (*κ* = 0.89, 0.94, and 0.88, respectively) [21, 36]. The validity for the Glasgow Coma Scale, however, remains controversial with some stating that the validity has been well established [37], while others question how the scale is assessed under different conditions such as sedation or intubation [36]. Pain will be assessed using the Numeric Rating Scale with an interrater reliability score of *κ* = 0.71 [23] and the Behavioural Pain Observation Tool which has a *κ* = 0.80 and a content validity index of 0.73–1.0 [24].

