### Methods for additional analyses (e.g. subgroup analyses) {20b}

Using data from movement patterns from a subgroup of participants (*n* = 100), non-supervised machine learning techniques will be applied to try to train a model to predict the onset of delirium. This subgroup will be used to address the secondary objective aimed to evaluate differences in movement patterns and intensity between the intervention and control group and between participants with delirium and without delirium.

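### The delirium label used to judge movement as a marker itself scores agitation or retardation, so part of any contemporaneous movement–delirium association is built in

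*Protocol article*

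**What the plan says.** Delirium has one operational definition. Section {18a} says "Delirium is assessed using the ICDSC". Outcomes {12} lists the features, "delirium is determined by consciousness, inattention, disorientation, hallucination, agitation or retardation, speech and mood, sleep/wake cycle disturbance, and fluctuation", and gives the threshold: "A unique incidence of delirium is counted once a patient reaches a score of ≥ 4, on a scale from 0 to 8". Eight listed features on a 0–8 scale imply one point per feature; the article does not say so in those words.

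Movement is then studied against that label. Outcomes {12} makes "the pattern and intensity of movements, before and during delirium as well as between groups" a secondary outcome and says that motor fluctuation "could be a possible marker for delirium detection". Objectives {7} expects to "identify patterns indicating the presence or absence of delirium". Section {20b} uses the first 100 participants to "evaluate differences in movement patterns and intensity between the intervention and control group and between participants with delirium and without delirium", and says that "non-supervised machine learning techniques will be applied to try to train a model to predict the onset of delirium".

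No second reference diagnosis of delirium is named, and no label that leaves out the motor item is described. The only check on the label is in the Discussion, where ICDSC scores are to be compared with the Richmond Agitation Sedation Scale. That scale also rates agitation, so the comparison does not remove the overlap.

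**The concern.** A participant with exactly three of the seven other features is labelled delirious if the nurse scores the motor item, and not delirious otherwise. Such a participant enters one comparison group or the other because of how much they move, and movement is then compared between the groups. Some difference is expected even if movement says nothing about attention, orientation, hallucination or the other features. Splitting cases into hyperactive, hypoactive and mixed delirium does not remove this.

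At stake is the reading of one of the trial's two main aims (Background and rationale {6a}). A movement difference or a model that discriminates could mean that sensors carry information about delirium at large, or only that they recover an item the nurse has already scored. The planned analysis cannot separate the two.

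**Working it through.** The documents give no figure on this point, so there is none to reproduce. The size is illustrated with a null model.

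**Inputs from the article**
- Label: score of at least 4 on eight items, one of them motor (Outcomes {12}).
- Proportion delirious: the mean of 39% and 30% (Sample size {14}), (0.39 + 0.30)/2 = 0.345.
- Sensor participants: n = 100 ({20b}), so 34.5 delirious and 65.5 not on average.

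**Assumptions, not in the article**
- S, the count of the seven other items, is beta-binomial with inter-item correlation 0.1, 0.2, 0.3 or 0.5.
- M, the motor item, is present with probability m = 0.2 to 0.5 and is independent of S. This is the null: movement carries no information on the other features.
- There is one label per participant. The item mean is solved so that P(D) = P(S ≥ 4) + m × P(S = 3) = 0.345.

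**Formulas**
- P(M | D) = m × P(S ≥ 3) / P(D)
- P(M | not D) = m × P(S ≤ 2) / (1 − P(D))
- Share of cases that are cases only through M = m × P(S = 3) / P(D)
- AUC of a yes/no marker = 0.5 + (difference in the two proportions)/2

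**Worked example: correlation 0.2, m = 0.4**
- The solved distribution has P(S ≥ 4) = 0.282, P(S = 3) = 0.158 and P(S ≥ 3) = 0.440. Check: 0.282 + 0.4 × 0.158 = 0.345.
- P(M | D) = 0.4 × 0.440/0.345 = 0.51, and P(M | not D) = 0.4 × 0.560/0.655 = 0.34.
- The odds ratio is 2.0, and the AUC is 0.5 + (0.510 − 0.342)/2 = 0.58.
- Cases only through M: 0.4 × 0.158/0.345 = 18%.
- A two-sided 5% test of two proportions with 34.5 and 65.5 participants rejects in 0.37 of studies.
- If the sensor reads the motor item with 80% sensitivity and specificity, the proportions become 0.8 × 0.510 + 0.2 × 0.490 = 0.506 and 0.8 × 0.342 + 0.2 × 0.658 = 0.405. The odds ratio is about 1.5, the AUC 0.55 and the rejection rate 0.16.

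**Full grid**

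| Sensor reading of the motor item | Odds ratio | AUC | Rejection rate (nominal 0.05) |
|---|---|---|---|
| Perfect | 1.41–2.47 | 0.53–0.61 | 0.11–0.56 |
| 80% sensitivity and specificity | 1.17–1.71 | 0.52–0.57 | 0.07–0.24 |

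Cases that are cases only through the motor item make up 5% to 29% of all cases over the grid.

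**Second model as a cross-check.** Here the other seven items share a latent factor with correlation 0, 0.3 or 0.5. The motor item is as frequent as the others and independent of them. With a perfect reading the built-in AUC is 0.65, 0.58 and 0.56. When the label is rescored on the seven other items at 4 or more, the AUC is 0.50 in each case, so the excess comes from the scoring rule alone. The proportion delirious falls from 34.5% to 24%, 29% and 30%.

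**The case against.** The strongest reply is that motor change belongs to delirium. The Background describes hypoactive, hyperactive and mixed forms, and detecting a component of a syndrome is a legitimate aim. This stands, and it is why the ICDSC threshold should remain the main label.

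Further points on that side also stand:
- No sensor output feeds the ICDSC. The label uses a nurse's rating; the tested quantity is acceleration at 100 Hz ({18a}). What is shared is the construct, not the data.
- Part of the aim is prediction of onset. Movement before the first positive score is not what the nurse rates at that later assessment, so the overlap is weaker there. The cross-sectional model above does not describe that case.
- The item counts agitation and retardation alike, so a one-directional intensity measure may pick up less of the overlap.
- Independence of the motor item from the other seven is a device to isolate the built-in part. Nothing in the article suggests that it is true.
- An AUC of 0.52 to 0.61 is weak discrimination and would not by itself yield a persuasive model.

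It can also be said that an article leaves sensitivity analyses to the full protocol or analysis plan. But the label, the marker and the comparison are fixed in this article, and its discussion of ICDSC validity offers only a cross-check that shares the problem.

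A reader might infer that any movement–delirium finding would be an artefact, or that the clinical need in the Background, delirium that goes unrecognised, would not be tested at all. The documents support neither. The Background ties missed cases to hypoactivity and somnolence, and continuous recording of reduced movement bears on exactly that.

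**Conclusion.** The point holds as an interpretive weakness of a secondary objective. For movement during delirium, and for participants with versus without delirium, the label and the marker share a feature, and the plan cannot show how much of an association goes beyond it. For prediction of onset the overlap is weaker. The VR-versus-control movement comparison and the primary test are not affected by this overlap in itself.

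The direction follows from the scoring rule whenever the motor item can carry a participant over the threshold and sensors read that item better than chance. The size rests on assumed item frequencies, correlations and sensor accuracy. The built-in AUC is modest, but with 100 participants a test could reject well above 5% of the time, from slightly above nominal to roughly half of studies over the range examined. This is a cheap improvement worth making; it does not invalidate the design.

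**What to change.** In Outcomes {12} and section {20b}:
- Keep an ICDSC score of 4 or more as the main delirium label.
- Export ICDSC item scores, not only totals, for the 100 sensor participants.
- Pre-specify a sensitivity analysis that repeats the movement comparison and the model with the label rescored without the agitation-or-retardation item: at least 4 of 7, with at least 3 of 7 as a second cut.
- Report both results side by side. Limit any claim that movement carries information beyond the motor item to what the second analysis supports. It should not be a pass/fail gate for calling movement a marker.

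The cost is the item-level export and a rerun of the same analysis. There are three downsides. At 4 of 7 there are fewer cases (24.5% to 32.9% of participants over the beta-binomial grid, against 34.5%). Neither cut-off is validated. And remaining items, such as sleep/wake disturbance, may still relate to movement, so the rescored label reduces the overlap but may not remove it fully.

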Other pre-specified outcome variables include physiological parameters, feasibility of using the VR stimulation by ICU nurses, cognition at ICU discharge and 6 months post-discharge, health-related quality of life and functional independence before ICU admission and 6 months post-discharge, disease-related data, and survival 6 months post-discharge from the ICU. Physiological parameters (e.g. blood pressure, heart rate, respiration rate) will be recorded continuously and changes from baseline, or the start of an event such as VR stimulation, will be compared to later time points. The changes occurring in these parameters over time, together with disease-related data, are of interest and could indicate what effect, if any, VR stimulation has on the condition of the participant. Scores for health-related quality of life, functional independence, and clinical frailty before ICU admission and 6 months post-discharge, and cognition before ICU discharge and 6 months post-discharge, will be compared to determine if any significant differences occur. Additionally, the average survival 6 months post-ICU discharge will be compared between groups. Looking at these variables between groups is important as cognition, health-related quality of life, independence, frailty, and mortality, among others, are known to be negatively impacted by the presence of delirium during the time spent in the ICU. Therefore, it is meaningful to identify if there were any significant changes in these aspects for individuals in the treatment group compared to the controls. It will also be important to determine if providing such an intervention is feasible for the care providers. For this, the validated System Usability Scale will be completed by the nurses in order to understand if overall, the use of this technology was accepted and whether or not it could be integrated into standard ICU care practices [29].

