Movement and movement patterns will be recorded continuously at 100 Hz for the duration of the participants’ stay in the ICU, with AX3 Axivity (Axivity Ltd., Newcastle upon Tyne, UK) inertial measurement units attached to participant’s hands, legs, and chest and placed under the mattress (Sensing Tex, Barcelona, Spain). To enable accurate interpretation of this data, the participant’s environment will be recorded with a camera. This will allow for the distinction to be made between movements made by the participant and those from the interprofessional team or family members. To maximize the privacy of the participant, the camera will be mounted on the head-end of the bed, so the face of the participant is not visible.

Physiological parameters (e.g. non-invasive arterial blood pressure, heart rate, and respiratory rate) will be monitored by the in-house monitor system of the University Hospital (GE Healthcare, Little Chalfont, UK). Respiration and heart rate will be measured at a frequency of 240 Hz, while the blood pressure will be measured as the median every 2 min. A list of pharmacological agents provided to the participant and disease-related data will be collected via the patient data management system. While movement and physiological data will be recorded continuously throughout the patients’ stay in the ICU, the non-continuous assessments will also be completed at various time points (Fig. 1).

At the earliest opportunity, the participant—or, in the event of incapacity, his/her relatives—will be interviewed by the study team about their health-related quality of life, functionality, and frailty, using the EQ-5D instrument [38], the Functional Independence Measure [39, 40], and the Clinical Frailty Score [41], respectively, 1 week before ICU admission and 6 months post-discharge. The reliability and validity of the three-level EQ-5D, the EQ-5D-3L, is well established; however, the more recently expanded five-level version, the EQ-5D-5L, still lacks proper reliability and validity studies [38]. The Functional Independence Measure has a reliability score of *κ* > 0.85 [42, 43] and a high internal validity [42]. The Clinical Frailty Score has been found to have good reliability [44] and good construct validity [41].

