## Statistical methods

### Statistical methods for primary and secondary outcomes {20a}

Descriptive statistics will be applied to both groups to ensure that they similarly represent the population. Among others, we will be looking at the mean and standard deviation of the age, distribution of the sexes, and frequencies of disease in the two samples.

The difference in the incidence of delirium will be tested with the chi-square proportion test, and the duration will be tested with Welch’s *t* test in subgroups of participants with delirium. The effects of the VR stimulation on physiological parameters will be looked at using statistical methods (e.g. *t* test, linear models). Machine learning techniques will be applied to the movement patterns as means of analysis.

The data will be analysed with MATLAB and the software R. Deviation(s) from the original statistical plan will be granted if the collected data do not allow the planned analysis techniques to be performed (e.g. if the collected data does not meet the prerequisites to apply analysis of variance techniques). In this case, more appropriate statistical methods will be applied (e.g. non-parametric methods), and this choice will be justified and detailed in the respective scientific reports.

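### The only comparison stated for physiological parameters is before-after within the patient, and it cannot by itself show an effect of VR; the article should commit to a comparison with the control arm

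*Protocol article*

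**What the plan says.** Objectives {7} lists, as the first of the further objectives, "evaluating the effect of VR stimulation, identified by changes in physiological parameters". Outcomes {12} places physiological parameters (blood pressure, heart rate and respiration rate are the examples) among the other pre-specified outcomes. It describes the comparison as "changes from baseline, or the start of an event such as VR stimulation, will be compared to later time points", and says that these changes over time, taken with disease-related data, "could indicate what effect, if any, VR stimulation has on the condition of the participant".

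Statistical methods {20a} adds one sentence: "The effects of the VR stimulation on physiological parameters will be looked at using statistical methods", with a t test and linear models as examples. It does not say whether the test is paired or between arms, and it names no comparator.

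On data availability, Plans for assessment and collection of outcomes {18a} says: "While movement and physiological data will be recorded continuously throughout the patients’ stay in the ICU". That wording is not limited to one arm.

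**The concern.** Randomisation protects a comparison between arms. It does not protect a comparison of a patient with the same patient earlier. Heart rate, blood pressure and respiration can change over half an hour of lying undisturbed, over the course of a day, and over the days in which a critically ill patient recovers or worsens. A before-after change in VR patients contains all of this as well as any VR effect.

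If the analysis followed the stated comparison and nothing more, a fall in heart rate during sessions could be reported as an effect of VR even if control patients showed the same fall over the same half hour. The trial would then have answered a named objective without its randomised comparator, although the monitor data for that comparator appear to be recorded in any case.

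**Working it through.** **1. What each form of the stated comparison can identify.** Write the mean change in VR patients as drift + effect, where drift is the change that would have occurred without VR. The mean change in control patients over a matched window is drift alone.

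- From the start of a session to later: only VR patients have a session start. The before-after mean estimates drift + effect. The two parts separate only if a control window is defined, and the article defines none.
- From baseline to later: both arms have a baseline. Within VR patients the mean again estimates drift + effect, with drift now covering recovery over a stay of up to 14 days. Subtracting the control mean leaves the effect: (drift + effect) − drift = effect. The data allow this, but the sentence in Outcomes {12} does not ask for it.

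**2. How the article words other outcomes.** In Objectives {7}, the objective on cognition, quality of life and functional independence is explicitly about differences between groups. The objective on physiology is worded as change. In Outcomes {12}, movement is to be compared before and during delirium and also between groups, and survival is to be compared between groups. The sentences that deal with physiology contain no such phrase.

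**3. Size, by illustration.** The article gives no standard deviation, drift or effect size for physiology, and its sample size rests on the primary outcome only, so there is no figure of the plan's own to reproduce here. Assume a true VR effect of zero, one change score per VR patient, and a background drift of k standard deviations of that change. For a two-sided paired test at 0.05, by normal approximation:

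λ = k × √n, and P(significant) = Φ(λ − 1.96) + Φ(−λ − 1.96).

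Take n = 460, the planned size of one arm (Sample size {14}), and n = 50, the number per group at the interim look, to show a small sample.

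| Drift k (SD of the change) | n = 50: λ | P(significant) | n = 460: λ | P(significant) |
|---|---|---|---|---|
| 0.1 | 0.71 | 11% | 2.14 | 57% |
| 0.2 | 1.41 | 29% | 4.29 | 99% |
| 0.3 | 2.12 | 56% | 6.43 | >99.9% |

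In concrete units, assume a standard deviation of 8 beats per minute for the 30-minute change in heart rate. A drift of 1 beat is k = 1/8 = 0.125 and a drift of 2 beats is k = 2/8 = 0.25. With the noncentral t distribution, n = 100 gives 24% and 70%, and n = 460 gives 76% and over 99.9%.

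The nominal rate is 5%. A comparison of change between arms over matched windows would hold that rate, because drift has the same expectation in both arms under randomisation. Using several sessions per patient does not rescue the paired test: averaging a patient's sessions reduces noise but leaves a drift common to the sessions in place.

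**The case against.** The strongest reply is that the article never says the control arm is left out. Four parts of it stand.

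- The stated comparison includes change from baseline, which exists in both arms, so it is not confined to VR sessions.
- Physiological parameters come first in the list of other outcomes in Outcomes {12}, and the same section later says: "Looking at these variables between groups is important as cognition, health-related quality of life, independence, frailty, and mortality, among others". The list is open-ended, and the text goes on to compare the treatment group with controls. Physiology is not named there, and the reason given is that delirium worsens the listed outcomes, so this does not establish a between-arm analysis of physiology. It does leave one possible.
- A t test or a linear model can be a two-arm analysis, and a full protocol or analysis plan that is not shown may specify one. Windows and adjustment are properly left to such a document.
- The inference is hedged, the objective is a further one, and neither the sample size nor the rule for declaring superiority depends on it.

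Two stronger readings are therefore not supported. A reader might infer that the trial will not use its control arm for physiology, or that its data cannot separate VR from rest and recovery. The article is silent on the first. The second is true of the before-after comparison alone, not of the data.

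A reader might also infer that sessions will be timed for when a patient is settled, which would select the starting values. No passage says so: sessions are part of the daily schedule. The article does say that sessions may be shortened according to the participant's reaction and that delirious participants may not tolerate the headset. That is a reason to include every scheduled slot in the analysis, but it is not evidence of selective timing.

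What remains is not a missing detail. The article does state a comparison and does attach an inference about VR to it, and that comparison does not support that inference.

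**Conclusion.** The point holds in a limited form. The one comparison spelled out for physiology is before-after within the patient, an effect of VR is to be read from it, and on that comparison alone the effect is confounded with undisturbed rest, time of day and recovery. The control arm is not excluded, but nothing commits the trial to using it for this objective.

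The size depends on a background drift that the documents do not give. Even a drift of 0.1 standard deviations would make a paired test significant in more than half of trials of the planned size with no VR effect at all. These figures apply only if the paired comparison is the one carried out and is read as an effect of VR.

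This is worth correcting, but it concerns an exploratory outcome. The conclusion on delirium incidence is untouched.

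**What to change.** State in Outcomes {12} and in Statistical methods {20a} that the effect of VR on physiological parameters is judged between the randomised arms:

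- For each scheduled morning, midday and evening slot, compare the change over the slot in VR patients with the change over the same clock-time window on the same study day in control patients, taken from existing monitor data.
- Adjust for the pre-slot value and allow for repeated slots per patient, for example with a mixed model that has a random patient effect.
- Include all scheduled slots in the VR arm, also those refused or shortened.
- Compare change from baseline between arms in the same way.
- Keep before-after summaries within the VR arm as descriptive only.

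The cost is a few sentences of wording, extraction of control windows from the monitor system, and a somewhat larger analysis. There is no new measurement and no added burden on patients.
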